### Intervention

The study participants will be allocated to one of these strategies:
Group 1: Standard management consisting of parental accompaniment during the preoperative period, post-anaesthesia recovery area and up to hospital discharge.Group 2: Standard management combined with distraction and accompaniment by [name] during the preoperative period, post-anaesthesia recovery area and up to hospital discharge. The clown will be present with the children during the post-anaesthesia period and up to discharge.Group 3: Standard management combined with pharmacological intervention (oral hydroxyzine 2 mg/kg masked with 5 ml of juice, administered at least 30 min prior to surgery).Group 4: Standard management combined with accompaniment and distraction by [name] and hydroxyzine (as described in the previous groups).

All the patients will be filmed in order to later evaluate the patient’s state of anxiety by the m-YPAS scale. Cortisol levels in saliva (using Salivette®) and blood will be also analysed for all subjects.

### Blinding

In order to hide clown accompaniment to the evaluator of the m-YPAS, their appearance on the screen will be avoided and the film will be silenced. Subjects in whose film [name] appears will be withdrawn from the study. The evaluation of all films will be done by the principal investigator.

Regarding hydroxyzine, the non-blinded nurse will administer 5 ml of juice to all subjects, mixed or not with hydroxyzine, depending on the treatment arm assigned.

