### Randomisation

Following signature of the IC by the legal guardians of the minors and/or the child’s agreement (if applicable), randomisation to treatment with/without hydroxyzine will be performed. Randomisation will occur in a 1:1 ratio in blocks of 8. The non-blinded nurse will randomise subjects with electronic case record form (REDCap). The sequence will be blinded to all team members.

Accompaniment by clowns ([name] from Fundacion Theodora) will depend on the clown presence/availability on the day of the intervention. An alphabetical code will be assigned to patients assigned to clown accompaniment (A) or not (B).

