### Treatment guideline

On the day of surgery, once the IC and, if applicable, child agreements have been signed and the selection criteria have been confirmed, the non-blinded nurse will randomise the subjects. Juice, with or without hydroxyzine, will be administered to subjects at least 30 min prior to the subject being transferred to the surgical ward.

POA evaluation will be performed at the following time-points:
Time-point 0 (M0): Considered the baseline status because it is the moment when the patient arrives to the pre-surgical hospitalisation area prior to being in contact with any method to reduce POA. At this time-point, the investigators will record a film in order to evaluate the patient’s baseline state of anxiety by the m-YPAS.Time-point 1 (M1): During the stay in the pre-surgical hospitalisation area, at least 30 min after receiving the assigned strategy. At this moment, investigators will record a film to later evaluate the subject’s preoperative state of anxiety by the m-YPAS. The first Salivette® will be provided to the patient for the collection and determination of salivary cortisol. Salivette® will be collected before leaving the pre-surgical hospitalisation area.Time-point 2 (M2): Moment when the patient is transferred to the operating room up to the entrance to the surgical ward and parental separation. The investigators will record a film during the transfer to the operating room and up to the entrance to the surgical block to later evaluate a subject’s preoperative anxiety by the m-YPAS scale. At this time-point, the second Salivette® will be collected when the patient is placed in the operating room bed.Time-point 3 (M3): During the induction of anaesthesia in the operating room: The investigators will record a film during the induction of anaesthesia to later evaluate subject’s preoperative anxiety by the m-YPAS scale. At this time-point, the anaesthesiologist will complete the Induction Compliance Checklist and a blood sample (5 ml) will be obtained for cortisol analysis.Stay in Post-Anaesthetic Care Unit (PACU): Upon arrival at PACU and until recovery from anaesthesia, the variables about recovery from anaesthesia, pain, delirium, vital signs and postoperative analgesia will be collected.Stay in General Ward: at the time of hospital discharge, parents/legal guardians will complete satisfaction survey as will children aged 5 years or older. Healthcare professionals will complete this survey at the end of the study.

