## Discussion

POA is observed amongst children during their stay in the operative room with a prevalence of 83.3% [23]. Adverse psychological and behavioural changes (decrease in children’s self-esteem and emotional well-being, increased anxiety, sleep disturbances and social isolation) have been observed in a rate of 25% in children during hospital stay and even at 1-year post-discharge [6]. A recent systematic review also identified negative psychological sequelae in children [18].

The search for an ideal premedication drug to reduce POA in children is ongoing. The drugs used as anxiolytics are not exempt of side effects and the studies about this issue are limited to dental procedures [14–16]. One study [15] evaluated hydroxyzine at doses of 0.15 mg/kg, yet the dose proposed in our clinical trial is of 2 mg/kg.

The role of clowns and hydroxyzine in the management of anxiety is controversial as there are studies both for and against them [18–20]. We have not found any study that determines the additive effect on anxiolysis of distracting techniques with clowns and pharmacological treatment, as we propose in our case.

The proposed study has some limitations. The clowns are not always at the hospital; therefore, assignment to this intervention depends on whether they are present or not on the day of surgery. In order to reduce this bias, the healthcare professionals that plan the patient’s surgery will not know when the clowns come to the hospital.

The main objective of this study is the evaluation of POA. Studies that evaluate POA are difficult to perform and interpret, mostly because of the difficulty in assessing anxiety attributable to the surgical act. According to some studies [3, 25], the moment with the maximum rate of anxiety and fear associated with the entire surgical procedure is during anaesthetic induction. Therefore, evaluating the child’s anxiety during anaesthetic induction is very useful to determine whether the strategies used in the presurgical period have been effective in reducing anxiety [26]. That is the reason why in the present study, POA is evaluated in both moments. Most studies on this topic use a presurgical anxiety rating scale, the m-YPAS [23, 24, 26, 27].

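### Keeping the clown off screen and silencing the film does not secure blinding of the sole m-YPAS rater, because clown status follows the day of surgery and only the surgery planners are kept from the clown calendar

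*Protocol article*

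**What the plan says.** All places are in the protocol article.

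- **Blinding.** The aim is to hide clown accompaniment from the m-YPAS evaluator. Two means are given: "their appearance on the screen will be avoided and the film will be silenced". If the clown does appear in a film, the child "will be withdrawn from the study". One person scores everything: "The evaluation of all films will be done by the principal investigator".
- **Randomisation.** Only hydroxyzine is randomised. Clown accompaniment "will depend on the clown presence/availability on the day of the intervention". Each patient gets a letter, A for clown and B for no clown.
- **Trial design.** There is one centre, and double blinding is claimed for the drug only.
- **Treatment guideline.** Films are made at M0, M1, M2 and M3 and scored later. The filming is done on site by the study team; for M3, "The investigators will record a film during the induction of anaesthesia".
- **Discussion.** The dependence on clown days is acknowledged as a limitation. The stated remedy is that the professionals who plan surgery "will not know when the clowns come to the hospital". The same section calls m-YPAS the subjective outcome and cortisol the objective one.

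**The concern.** Hiding the clown within the frame works only if clown status cannot be learned in another way. Here it follows the day of surgery, so it can be inferred from a film's date by anyone who knows which days had clowns, or from having been present that day. Under Intervention, the clowns stay with the child through recovery and up to discharge, so site staff can see them. The person chosen to score every film leads the trial at that one site. The only stated concealment of clown days covers a different group of people, the surgery planners.

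What is at stake is the clown part of the trial. The main objective, at the end of the Background, is whether hydroxyzine and clowns have an additive effect, and m-YPAS is the outcome on which the sample size rests. Randomisation does not protect the comparisons that differ in clown status, so masked scoring is one of their few safeguards.

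**Working it through.** **1. The plan's own figure.** Inputs from Sample size: means 32.3 and 18 (difference 14.3), SDs 24.2 and 13.5, 47 per group, power 90%, significance level 0.025.

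- Average variance = (13.5² + 24.2²)/2 = (182.25 + 585.64)/2 = 383.9, so SD = 19.6.
- n per group = (2.241 + 1.282)² × (182.25 + 585.64)/14.3² = 46.6, rounded up to 47.

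This reproduces the stated 47, with 0.025 read as two-sided. The sample size is not in question.

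**2. Which comparisons a tilt can reach.** Let *b* be the average number of points by which a rater who knows the clown status scores clown-day children differently. Groups 2 and 4 have the clown; Groups 1 and 3 do not.

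| Comparison | Effect of a tilt *b* that is constant over films |
|---|---|
| Group 2 v 1, 4 v 3, 4 v 1 at one time-point | shifted by *b* |
| Group 3 v 1, 4 v 2 | cancels (same clown status) |
| Within-child change between two moments | cancels |
| (4 − 3) − (2 − 1), the interaction | cancels if *b* is equal in both drug arms |
| Cortisol | none; it is not scored from film |

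Sample size describes a comparison of induction with the moment before entry to the operating room. Data analysis plans a repeated measures ANOVA with a group interaction, and also a comparison of means at each time-point. The time-point comparisons are therefore exposed to a constant tilt. The change is exposed only if the tilt differs between moments. That is possible: the Background says clowns seem to help in the pre-surgical area but that benefit inside the surgical area is unproven, so a rater's expectation need not be the same at each moment.

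**3. Illustrative size.** The article gives no figure for rater tilt, so *b* is assumed. There is no true clown effect, 47 v 47, and two-sided alpha 0.025 (critical value 2.241).

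- SE = 19.6 × √(2/47) = 4.04.
- False-positive rate = Φ(−2.241 + *b*/SE) + Φ(−2.241 − *b*/SE).
- *b* = 0: 2.5%.
- *b* = 2: *b*/SE = 0.495; 0.0404 + 0.0031 = 4.3%.
- *b* = 4: *b*/SE = 0.990; 0.1053 + 0.0006 = 10.6%.

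The two SDs come from groups without a clown, so I repeated the calculation at each of them:

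| SD | SE | *b* = 2 | *b* = 4 |
|---|---|---|---|
| 13.5 | 2.78 | 6.5% | 21.1% |
| 19.6 | 4.04 | 4.3% | 10.6% |
| 24.2 | 4.99 | 3.7% | 7.6% |

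For scale, the planning difference is 14.3 points. A larger sample does not remove such a bias; it makes a given tilt more likely to reach significance.

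**The case against.** A reader might infer that the rater is in fact unblinded. The article does not support that. Nowhere does it say that the principal investigator films, attends, sees film dates, holds the A/B code or knows the clown days. A date alone reveals nothing without the calendar, and a neutral letter code may itself be meant as masking. That all children on one day share the same clown status is an inference from how exposure is determined, not a stated fact. This stands, and it limits the conclusion to blinding that is not secured.

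A second objection is that a journal article condenses a full protocol, and that file coding, clip order and score locking are commonly left to that document. This stands for those details, and their absence is not the point here. The point rests on what the article does state: its masking goal, its means, its choice of the site's lead investigator as sole rater, and a concealment of clown days limited to surgery planners.

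A third objection is that the false-positive rates rest on an assumed constant tilt, and that such a tilt cancels in the within-child change and in the drug comparison for which the trial is powered. Both are correct, so the figures apply only to the time-point comparisons that differ in clown status. Cortisol also gives an outcome that is free of the rater. It does not, however, correct the m-YPAS result.

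**Conclusion.** The concern holds in a limited form. The stated masking does not secure the goal that the Blinding section sets for itself, on an outcome the article calls subjective. Bias is possible and not shown. It would need a rater who knows the clown status and leans on that knowledge. It would then affect Group 2 v 1, 4 v 3 and 4 v 1 at single time-points, and the change scores only if the lean differs between moments. Group 3 v 1 and 4 v 2 are not affected by a constant tilt, nor is cortisol affected at all.

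The size is illustrative: a false-positive rate of 4.3% for a 2-point tilt and 10.6% for a 4-point tilt, against a nominal 2.5%. This assumes SD 19.6, 47 independent children per group, no true clown effect and two-sided 0.025. The weakness should be corrected because the films are scored after recording and better masking needs no extra reader.

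**What to change.** Amend the Blinding section as follows, keeping the single rater.

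1. Staff who are already unblinded, for example the non-blinded nurse, remove date, study number and A/B code from the film files, number the clips at random, and present them in random order across children and days.
2. The rater has no access to the clown calendar or the A/B code.
3. Scores are locked before they are linked to group.
4. For films already scored, a random coded sample is re-scored in this way and agreement is reported by clown status.
5. The report states which children the rater filmed or attended, and the clown comparisons are repeated without them as a sensitivity analysis.

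The cost is file-handling work, one paragraph of text and limited re-scoring time. Re-scoring everything could mean 188 × 4 = 752 films, which is why a sample is proposed. Two limits remain. Coding cannot remove a child's face, so a rater who saw the child may still recognise the child. Trial status also gives 30 December 2019 as the end of recruitment, so a rule against attending would come too late for children already filmed; item 5 is there for that reason.

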### Treatment guideline

On the day of surgery, once the IC and, if applicable, child agreements have been signed and the selection criteria have been confirmed, the non-blinded nurse will randomise the subjects. Juice, with or without hydroxyzine, will be administered to subjects at least 30 min prior to the subject being transferred to the surgical ward.

POA evaluation will be performed at the following time-points:
Time-point 0 (M0): Considered the baseline status because it is the moment when the patient arrives to the pre-surgical hospitalisation area prior to being in contact with any method to reduce POA. At this time-point, the investigators will record a film in order to evaluate the patient’s baseline state of anxiety by the m-YPAS.Time-point 1 (M1): During the stay in the pre-surgical hospitalisation area, at least 30 min after receiving the assigned strategy. At this moment, investigators will record a film to later evaluate the subject’s preoperative state of anxiety by the m-YPAS. The first Salivette® will be provided to the patient for the collection and determination of salivary cortisol. Salivette® will be collected before leaving the pre-surgical hospitalisation area.Time-point 2 (M2): Moment when the patient is transferred to the operating room up to the entrance to the surgical ward and parental separation. The investigators will record a film during the transfer to the operating room and up to the entrance to the surgical block to later evaluate a subject’s preoperative anxiety by the m-YPAS scale. At this time-point, the second Salivette® will be collected when the patient is placed in the operating room bed.Time-point 3 (M3): During the induction of anaesthesia in the operating room: The investigators will record a film during the induction of anaesthesia to later evaluate subject’s preoperative anxiety by the m-YPAS scale. At this time-point, the anaesthesiologist will complete the Induction Compliance Checklist and a blood sample (5 ml) will be obtained for cortisol analysis.Stay in Post-Anaesthetic Care Unit (PACU): Upon arrival at PACU and until recovery from anaesthesia, the variables about recovery from anaesthesia, pain, delirium, vital signs and postoperative analgesia will be collected.Stay in General Ward: at the time of hospital discharge, parents/legal guardians will complete satisfaction survey as will children aged 5 years or older. Healthcare professionals will complete this survey at the end of the study.

Subjects will exit the study at hospital discharge.

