**Methods:**

We propose a randomised double-blind, controlled clinical trial that will evaluate the effectiveness of both interventions (hydroxyzine and clowns), alone or in combination, to reduce pre-operative anxiety (using the modified Yale scale of preoperative anxiety) in children aged 2–16 years undergoing outpatient surgery (*n* = 188).

Subjects will be randomised into two groups – (1) standard procedure (parental accompaniment) combined with placebo or (2) standard procedure combined with preoperative hydroxyzine. After randomisation, they will be divided by chance into two further groups, depending on the presence of clowns on the patient’s surgery day. Control of pre-operative anxiety will be determined in the four groups by a modified Yale scale of preoperative anxiety and cortisol levels. Compliance of children during induction of anaesthesia, time until anaesthesia recovery, presence of postoperative delirium and use of analgesia until discharge will be also assessed. For additional information, the children, parents and healthcare professionals involved in the study will complete a satisfaction survey.

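### Clown status is settled on the surgery day before the child is entered, and the one stated safeguard covers only those who plan surgery, so selective entry could bias the contrasts that cross clown status

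*Protocol article*

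**What the plan says.** All references are to the protocol article.

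- **Clown allocation (Randomisation).** Clown accompaniment "will depend on the clown presence/availability on the day of the intervention". The Discussion lists this as a limitation: "assignment to this intervention depends on whether they are present or not on the day of surgery".
- **Entry (Treatment guideline).** The nurse randomises "On the day of surgery, once the IC and, if applicable, child agreements have been signed and the selection criteria have been confirmed". Eligibility confirmation and randomisation fall on the surgery day. Consent may be signed then or earlier.
- **Drug allocation (Randomisation).** "The non-blinded nurse will randomise subjects with electronic case record form (REDCap"), and "The sequence will be blinded to all team members". This sequence decides hydroxyzine or placebo only.
- **Safeguard on clown days (Discussion).** To reduce the bias, "the healthcare professionals that plan the patient’s surgery will not know when the clowns come to the hospital".
- **Abstract, Methods.** "After randomisation, they will be divided by chance into two further groups". The same sentence adds that the split depends on whether clowns are there on the surgery day.
- **Baseline and analysis.** M0 is filmed on arrival, before the child meets any anxiety-reducing method. The Data analysis section compares the four groups at baseline, adjusts if clinically relevant differences appear, and uses repeated-measures ANOVA with a study-group interaction.

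**The concern.** Someone who knows which arm the next child will fall into can let that knowledge affect whether the child is entered. Concealment exists to prevent this. For the clown factor there is no sequence to conceal, because the calendar day decides, and entry is completed on that same day. Hiding the clown days from surgery planners protects the choice of date. It does not protect the later decision to approach, consent or enter a child.

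The two routes are separate. Even with perfectly blind scheduling, the children who enter on a clown day may differ from those who enter on another day. For example, a family that likes clowns may agree more readily when one is in the building, and a family whose child fears them may decline.

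The main objective, in the Background, is whether hydroxyzine and clowns have an additive effect. The contrasts of group 2 v 1, 4 v 3 and 4 v 1 all cross clown status, so they would carry any such difference. Randomising hydroxyzine does not remove it. It protects only the drug contrast within clown days and within non-clown days.

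**Working it through.** **Step 1. Does any stated measure conceal clown status at entry?**

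| Measure | Section | What it protects |
|---|---|---|
| Surgery planners unaware of clown days | Discussion | Choice of surgery date |
| Blinded sequence | Randomisation | Hydroxyzine or placebo allocation |
| Double blinding, drug only | Trial design | Drug allocation |
| Silenced films without clowns | Blinding | Scoring of m-YPAS |
| M0 before contact with any method | Treatment guideline | Baseline score, not knowledge of clown presence |

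None covers those who approach, consent or confirm eligibility, or the families.

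**Step 2. The plan's own figure.** The inputs, from Sample size, are a difference of 14.3 points, SDs of 13.5 and 24.2, 90% power and significance level 0.025. Taking the level as two-sided:

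n = (13.5² + 24.2²) × (2.241 + 1.282)² / 14.3² = 46.6, rounded up to 47 per group.

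The stated 47 is reproduced. It has no bearing on concealment, but it supplies the group size and SD used below.

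**Step 3. Illustrative shift in the clown-group mean.** The article gives no entry rates, so these are assumptions: a share c0 = 0.70 of eligible children enters on non-clown days and c1 = 0.80 or 0.90 on clown days. The extra entrants differ from the others by k = 0.5 or 1 SD, with SD = 24.2 (parental accompaniment group).

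Shift = (c1 − c0)/c1 × k × 24.2

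- c1 = 0.80, k = 0.5: 0.125 × 12.1 = 1.5 points
- c1 = 0.80, k = 1: 0.125 × 24.2 = 3.0 points
- c1 = 0.90, k = 0.5: 0.222 × 12.1 = 2.7 points
- c1 = 0.90, k = 1: 0.222 × 24.2 = 5.4 points

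Against the planning difference, 1.5/14.3 = 11% and 5.4/14.3 = 38%.

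**Step 4. False-positive rate with no true clown effect.** For 47 v 47 with SD 24.2 in both groups, SE = 24.2 × √(2/47) = 4.99. With a normal approximation and no adjustment for M0, the two-sided rejection rate is 1 − Φ(z − shift/SE) + Φ(−z − shift/SE).

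| Shift (points) | Shift/SE | Nominal 5% (z = 1.960) | Nominal 2.5% (z = 2.241) |
|---|---|---|---|
| 0 | 0 | 5.0% | 2.5% |
| 1.5 | 0.30 | 6.1% | 3.2% |
| 2.7 | 0.54 | 8.4% | 4.7% |
| 3.0 | 0.61 | 9.3% | 5.3% |
| 5.4 | 1.08 | 19.0% | 12.3% |

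Both levels are shown because Data analysis uses 5% and Sample size uses 0.025.

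**The case against.** **Visibility is inferred.** A reader might conclude that recruiters and families do see the clown before deciding, so that assignment is known with certainty at entry. The article does not say so. It shows that clown status is settled before entry and that no stated step hides it. Filming M0 before contact with any method may mean that clowns are kept away at arrival. What stands is that clown status can be known, not that it is.

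**Room for selection may be small.** Consent may precede the surgery day, in which case the family's decision comes before any sight of a clown. The inclusion and exclusion criteria are mostly factual (age, ASA grade, allergy, previous surgery, porphyria, QT risk) and leave little discretion. This narrows the route to who is approached, same-day consent and withdrawal of agreement. It does not close it.

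**The article is condensed.** It cites protocol version 7, which is not shown and may describe recruitment more fully. That is a fair caution. But the article itself names the bias and offers a remedy for it, and that remedy reaches only scheduling.

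**The analysis catches part of a shift.** A difference that is constant over time would cancel in the group-by-time interaction, and the baseline adjustment may pick up a visible imbalance. That adjustment is conditional, however, and the Demographics section lists only age, sex, underlying pathology and type of surgery. M0 reflects anxiety on arrival. It does not capture attitude to clowns or likely response to them.

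**The abstract discloses the mechanism.** It does, in the second half of its sentence. The first half still presents the split as chance following randomisation, which does not fit an assignment set by the day.

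**Conclusion.** The concern holds as a statement of what the design permits. Clown status is fixed on the surgery day before entry is complete, and the only stated safeguard stops at those who plan surgery. Selective entry could bias the contrasts of group 2 v 1, 4 v 3 and 4 v 1, and with them the combination claim. Hydroxyzine v placebo within a clown stratum is not affected by this route.

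The documents do not support the claim that selection has occurred, nor any estimate of its size. The range of about 6% to 19% rests wholly on assumed entry rates, an assumed difference of 0.5 to 1 SD, an SD of 24.2 in both groups and no adjustment. At the low end the inflation is slight, and M0 would reduce it further where the selection acts through baseline anxiety. The point merits action mainly because the remedy is cheap and the affected contrasts carry the main objective.

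**What to change.** 1. Extend the hiding of the clown calendar to those who approach, consent and confirm eligibility, and to families, until consent, entry and the M0 film are done.
2. Enter every consented, eligible child whatever the clown status.
3. Log eligible, approached and consented children by clown and non-clown day in REDCap, and report the counts beside each clown contrast.
4. Adjust the clown contrasts for M0 m-YPAS in all cases, not only when an imbalance is noticed.
5. Reword the abstract: the clown split follows clown availability on the surgery day and is not a division by chance after randomisation.

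**Cost.** Procedure wording, a screening-log field and one covariate, with no extra staff or patients. The downside is that clowns must stay out of the admission area until the M0 film is done. Recruitment was due to end on 30 December 2019 (Trial status). For children already enrolled, only the log (where records allow), the M0 adjustment and the rewording apply.
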